### Study interventions

The desire to implement group ANC in this setting required the reconsideration or customization of an intervention that has been well-defined in the context of trials in high-income economies. In most trials of group ANC, the intervention is the trademarked product CenteringPregnancy®
^21^, but for three reasons we did not assume that the existing intervention could be applied ‘off-the-shelf” in Rwanda. First, the number of visits in the CenteringPregnancy® package is greater than the number of visits recommended in the Rwanda ANC package; second, the last Demographic and Health Survey estimated that one-third of Rwandan women could not read or write well;
^17^ and finally, the unique language (Kinyarwanda) and cultural context called for customized discussion activities.

The Rwanda group ANC/PNC model was customized by the Technical Working Group, which is composed of representatives from maternal-child health stakeholder organizations in Rwanda; that model development process is described separately
^22^. Key characteristics of the Rwanda group ANC/PNC model appear in
Box 1. Despite the 2016 WHO ANC recommendations
^16^, the total number of ANC visits recommended in Rwanda is four. Of the four total PNC visits recommended in Rwanda, only PNC 4 (at approximately six weeks after birth) is a group visit. The other PNC visits do not lend themselves to a group arrangement and remain unchanged. PNC 1 is completed before facility discharge within 24 hours after delivery, and PNC visits 2 and 3 are conducted at home by community health workers.

Box 1. Key characteristics of group antenatal care (ANC) and postnatal care (PNC) model.1.Women sit in a circle in a group space where other staff and patients do not enter during the visit.2.Two co-facilitators lead each group visit: one ANC provider (midwife or nurse) and one Community Health Worker (CHW) with special training in maternal-child health.3.Confidentiality and mutual respect are prioritized by pregnant women and co-facilitators.4.Clean water is offered to the women to drink while they socialize during the first 30 minutes.5.Health assessments are conducted on a rolling basis during the first 30 minutes, as women arrive at the scheduled visit time.6.Women participate in their own health assessments as much as possible (blood pressure and weight measurements).7.Brief consultations, including assessments such as fundal height measurement, are conducted in a semi-private area of the group space.8.Women and newborns receive the routine assessments, screening, and treatments described in the Rwanda ANC/PNC packages, as well as treatments indicated for special conditions.9.Women are referred to the district hospital for abnormal conditions, according to current national guidelines. The doctor with whom a referred woman consults will develop a plan of care and indicate on the counter-referral form whether or not she should continue to attend ANC visits at the health facility.10.Group discussion begins after health assessments are completed and lasts 1 hour.11.Key messages consistent with Rwanda’s ANC and PNC packages are delivered through facilitated discussion.12.Learning activities are based on principles of adult education, including repetition, peer-to-peer teaching, and fun.13.Each group of women decides if they will invite husbands and next-of-kin to attend group visits.14.Co-facilitators “debrief” after every group visit in a continuous learning and quality improvement process.15.Women are invited to return to the health facility at any time for individual episodic evaluation of danger signs or any other concerns.

Group ANC and PNC visits are timed according to the schedule in
Table 1. This schedule places all group care visits eight weeks apart and simplifies group scheduling for the health facility. Those attending the first ANC visit in late in pregnancy are invited to attend the remaining scheduled visits of their assigned group (by estimated date of delivery, known as EDD) and are also invited to attend the visits they have missed with different groups as a ‘drop-in’ guest. It is ideal for a group of women to be entirely consistent over time; however, it is practical to plan for some movement of women between groups as needed. The goal is that by six weeks after birth women will meet for a final group visit with other mothers they already know and with whom they have formed close connections during group ANC.

**Table 1. T1:** Rwanda group antenatal care (ANC)/group postnatal care (PNC): visit timing and curriculum content.

Visit	Timing	Educational Content
ANC 1 (standard, one-on-one initial pregnancy visit)	Variable: ideal is before 16 weeks gestation	Standard (e.g. HIV counseling and testing) Introduction to group care model and invitation to participate
ANC 2 (1st group visit)	20–24 weeks	Nutrition, supplements, and harmful substances Pregnancy danger signs Infection prevention and treatment
ANC 3 (2 ^nd^ group visit)	28–32 weeks	Birth plan (includes signs of labor) Healthy birth spacing and family planning Maternal mental health Review pregnancy danger signs
ANC 4 (3 ^rd^ group visit)	36–40 weeks	Respectful maternity care Breastfeeding and newborn care Postnatal and newborn danger signs Review family planning Review pregnancy danger signs
PNC (4 ^th^ group visit)	Approximately 6 weeks after birth	Review breastfeeding and infant feeding Review newborn danger signs Preventing health problems (e.g. insecticide-treated nets, hygiene, immunizations) Newborn and infant cognitive development (sing, talk, read, play)

When a pregnant woman presents at any health facility randomized to either Arm 3 or Arm 4 for her first ANC visit (ANC 1), she will experience a standard individual visit with a provider. At the conclusion of the ANC 1 visit, if ongoing ANC at the health center is most appropriate for the pregnant mother, the provider will invite the woman to participate in group ANC. Individual visits will continue to be offered for women and newborns requiring episodic examination and management, and for those who may decline group care participation. After the ANC provider identifies the woman’s due date based on best obstetric estimate, a member of the study staff assigns the woman to a group of 8–12 women with similar due dates—within the same two-week period is preferred and within the same four-week period is acceptable. Once the woman has been assigned to a group, all the dates of her group ANC visits 2–4 and group PNC visit at six weeks are known and the study staff communicate these to her either all at once or one at a time (at each visit), based on the provider’s preference. All women enrolled in the trial—both at control and intervention sites—will be encouraged to give birth in a facility, where the first PNC visit is delivered, to seek PNC care from the community health workers (CHWs) when the newborn is about three days and seven days old, and to return to the facility for PNC when the newborn is about six weeks old.

In Rwanda, ANC and PNC services are provided at each health center by advanced diploma-level nurses; a minority of these nurses have qualified as midwives. If physician care is required, women are referred to the district hospital for advanced services. A robust network of CHWs with special training in and responsibility for maternal and newborn health have frequent village-level contact with pregnant women. These two groups of health care workers were selected to function as co-facilitators (one ANC/PNC provider and one CHW) of each group visit.

Those providers and CHWs associated with sites randomized to group ANC were invited to a three-day training workshop on a rotating basis to minimize the impact on service provision. This workshop brought providers and CHWs together in joint training activities for the first time ever. Training occurred in large- and small-group circles to replicate as closely as possible the principles of successful group care. Activities focused on principles of adult learning, facilitation skills, a review of the Rwanda ANC/PNC packages of care, health assessment skills, how to organize and facilitate a group visit, and role-play practice of each of the group ANC/PNC curriculum discussion topics with feedback and re-practice.

These new group ANC facilitators were trained in all aspects of model fidelity by a team of six Rwandan group ANC Master Trainers
^22^. The Master Trainers, five midwives and one physician, who all have separate employment, were recruited based on their excellent facilitation skills, expertise in maternal and newborn health, and commitment to the project. The Master Trainers will make scheduled visits to each health center providing group ANC, with decreasing frequency over time, and unscheduled visits will be made as needed. During these visits, Master Trainers will observe group ANC as it is delivered and collect data about model fidelity. They will also offer supportive feedback and will model for group ANC facilitators how to plan for and debrief after each visit.

Study sites assigned to either Arm 2 or Arm 4 are randomized to introduce basic obstetric ultrasound by ANC providers at the health center and urine pregnancy testing by CHWs in the community (
Figure 1). The objective of screening ultrasound at the health center level is to more accurately assign the EDD, but providers are also trained to screen for gross abnormalities. The goal of community-based pregnancy testing is to engage women in earlier ANC attendance, which in turn may identify and promote early referral of at-risk pregnancies for physician consultation at district hospitals.

Members of the Rwanda Society of Radiologists developed training materials, provided training in basic obstetric ultrasound examination, and defined a mentorship and quality assurance plan. Two to three ANC providers (nurses & midwives) from each health center in Arms 2 and 4 and one radiography technician from each of the six district hospitals attended a 10-day obstetric ultrasound course created for frontline health workers customized for this context. The hospital-based radiography technicians were invited to serve as on-site ultrasound mentors to the ANC providers at the health centers associated with each hospital catchment area. They will provide frequent on-site mentorship during the first months of ultrasound implementation and then conduct monthly mentorship visits through the remainder of the study period. Members of the Society of Radiologists will engage in quarterly onsite visits at health centers and will conduct quality control by remotely reviewing securely shared files that include US examinations and their reports. Women who seek ANC at health centers in Arms 2 and 4 are offered a basic screening obstetric ultrasound either on the day of their first ANC visit or soon after.

Over 700 CHWs assigned to support maternal and newborn care in the catchment areas of health centers in Arms 2 and 4 were trained to administer a projected 25,000 urine pregnancy tests (UPTs) per year. The UPT training curriculum was developed in Kinyarwanda and English by RBC, which will also procure and distribute UPT kits and gloves. Women who test positive for pregnancy in the community are referred to the health center for early ANC. The CHW supervisor associated with each health center will provide ongoing monitoring and supervision of community-based UPT activities and report to the health center on a monthly basis.

Participation in any of these three interventions—group care, obstetric ultrasound, and urine pregnancy testing—is voluntary for any potential trial participant. All women who present for the first ANC visit are invited to consent to participate in the trial, in any of the four arms. Women who have consented to participate in the trial can withdraw their consent at any time for any reason.

### Outcomes and processes for comparison

This trial will evaluate both outcomes and processes. The primary study outcome is GA at birth. GA at birth will be calculated using the EDD assigned by ANC providers using the best obstetric estimate. In health centers randomized to implement basic obstetric ultrasound, this tool will be used to optimize GA assignment. In addition, postnatal measurements of every newborn will be used to estimate GA at birth and assign a corrected GA if needed.

Secondary outcomes include attendance, PTB rate, and neonatal mortality and morbidity among preterm neonates. Outcomes, including analysis metrics, method of aggregation and time points are summarized in
Table 2.

**Table 2. T2:** Outcomes.

Measurements variable	Analysis metric	Aggregation	Time Point
Primary Outcomes			
GA at birth	Average weeks completed	Health center	At delivery
Secondary Outcomes			
Preterm birth	Yes/no <37 weeks GA	Rate compared across arms	At delivery
Mortality among preterm neonates	Alive/dead	Rate compared across arms	At 28 days and 42 days, measured at six week follow up visit
Attendance at four ANC visits	Yes/no	Proportion compared across arms	At Delivery
Attendance at ANC one <14 weeks GA	Yes/no	Proportion compared across arms	At ANC 1
Attendance at PNC at six weeks	Yes/No	Proportion compared across arms	Record review at 12 weeks post EDD
Women identified as being high risk at ANC	Yes/no	Proportion compared across arms	From 1 ^st^ ANC until day of delivery
Caesarean section	Yes/no	Proportion compared across arms	At delivery
Newborn morbidities: jaundice, rapid breathing, fever, pneumonia, hypothermia, cord infection	Any reported: Yes/no	Proportion compared across arms	Reported in Rapid SMS (community reporting system) or neonatal register by 28 days of age
Other Outcomes			
Acceptability	Qualitative data on acceptability to women and providers	Qualitative reporting	At nine and 18 months
Satisfaction with care, locus of control, perceived social support, perceived stress, and depressive symptoms	Survey data	Comparison across arms	Baseline (at enrollment) and eight weeks after birth
Postnatal health behaviors, including family planning uptake, insecticide- treated mosquito net use, and breastfeeding	Survey data	Comparison across arms	Eight weeks after birth

GA, gestational age; ANC, antenatal care; PNC, postnatal care; EDD, estimated date of delivery.

We will also report several descriptive results of interest and identify factors that influence uptake, fidelity, and sustainability of group care in Rwanda. This includes the proportion of ANC and PNC visits at sites randomized to group care that occur in a group versus one-on-one with a provider. We will describe attendance at group care visits by men or female ‘next of kin’. Uptake will be measured by enrollment and mothers’ attendance at scheduled group antenatal care (gANC) visits. Furthermore, a subset of women will be included in a participant survey at enrollment (during pregnancy) and after birth; we will measure satisfaction with care, locus of control, perceived social support, perceived stress, and depressive symptoms (see
*Extended data*: File 3)
^18^. The postnatal questionnaire (unpiloted) will also include questions about health behaviors such as breastfeeding, post-partum family planning and use of an insecticide-treated bed net (see
*Extended data*: File 4 and 5)
^18^.

Additionally, providers at both group ANC and standard ANC study sites will participate in a longitudinal survey, with questionnaires administered at baseline, nine, and 18 months (see
*Extended data*: Files 6–8)
^18^. Measures of interest include level of education and years of clinical experience, job satisfaction and preferences, and perceived stress. We will report the uptake and effects of introducing urine pregnancy testing by CHWs and ultrasound by primary ANC providers.

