**ANC 1 within 1st trimester**	Women who attended ANC 1 <16 weeks	All women who attended ANC 1	ANC Register
**Identification of high risk**	Women with risk factors identified Number of women referred with risk factors	All women who attended ANC 1	ANC Register
**Maternal morbidity**	Cesaerean sections women referred for delivery women 'sick'	All deliveries	MAT Register, Referral Forms, RapidSMS

GA, gestational age; LMP, last menstrual period; MAT, maternity; NEO, neonatal; ANC, antenatal care; PNC, postnatal care;.

Other secondary outcomes will be measured. First, to survey a sub-set of participants across all trial arms, a convenience sample of the first five women to present for ANC per month are invited to participate in a baseline questionnaire measuring satisfaction with care, locus of control, perceived social support, perceived stress, and depressive symptoms. Similarly, among those who present at the health center with newborns approximately six weeks after birth, five women will be invited to participate in a follow-up questionnaire in which the same baseline questions are repeated and additional questions about postnatal health behaviors, including family planning uptake, insecticide-treated mosquito net use, and breastfeeding, are added
*.* This will be an unmatched cohort of survey participants and the baseline and postnatal questionnaires (see
*Extended data*: Files 3–5)
^18^. These questionnaires will be conducted in person by the data collector when the woman visits the health facility. Second, ANC and PNC providers in all arms are invited to participate in a longitudinal survey about job satisfaction, preferences, and perceived stress (baseline and follow-up questionnaires are available as
*Extended data*: Files 6–8)
^18^. These data will be collected at study training meetings or administered by data collectors at the facilities. The baseline data of providers trained to deliver group ANC/PNC will be linked to their longitudinal scores of group ANC model fidelity assessed at regular intervals by the Master Trainers (assessment tool appears as
*Extended data*: File 9)

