## Discussion

In WHO’s 2016
*Recommendations on antenatal care for a positive pregnancy experience*, the authors write that

“communication and support functions of ANC are key, not only to saving lives, but to improving lives, health-care utilization and quality of care. Women’s positive experiences during ANC and childbirth can create the foundations for healthy motherhood.”
^16^

Group ANC seems to hold the promise of improved effectiveness of health message communication in a peer-to-peer education model, enhanced support and cohesion among pregnant women in a community, and increased satisfaction with and uptake of ANC.

This trial will provide much-needed evidence to advance the field. First, it will examine the health effects of group ANC in the context of low- and middle-income countries (LMICs) and within an intent-to-treat approach almost identical to routine health service delivery in that context. Second, it is the first to test group care as applied to the four-visit Focused ANC model widely used in LMICs, and thus will provide evidence about whether this innovative model can improve adherence to the four-visit schedule. Third, the trial will also report whether the group care model impacts attendance at six-week PNC in a context in which PNC attendance is currently very low. Fourth, the trial will also provide feasibility evidence regarding the use of CHWs as co-facilitators in group care. Lastly, this trial further provides additional insight into the relative effects of basic obstetric ultrasound at health centers and urine pregnancy testing at the community level on early uptake of ANC and adherence to the recommended visit schedule.

This is the largest trial of group ANC to date, powered to detect a difference in GA at birth. The implementation of group ANC at this scale within the practical realities of a national maternity care system will inform global stakeholders as they make decisions at the policy, system, facility, and individual levels about the optimal ANC service model for the mothers and newborns they serve.

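### Early ANC attendance can be dated with ultrasound in Arms 2 and 4 but not in Arms 1 and 3, and no common pre-scan dating source is fixed, so comparisons of the ultrasound and pregnancy-testing package can reflect dating instead of attendance.

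*Protocol article*

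**What the plan says.** All references are to the protocol article.

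- **Assignment.** Under Study design, one pair in each quadruple is randomised to receive both ultrasound and community pregnancy testing. The two components always travel together (Arms 2 and 4).
- **Purpose and timing of the scan.** Study interventions states: "The objective of screening ultrasound at the health center level is to more accurately assign the EDD". Women in Arms 2 and 4 are "offered a basic screening obstetric ultrasound either on the day of their first ANC visit or soon after". Participation is voluntary.
- **Dating.** Outcomes and processes for comparison states: "GA at birth will be calculated using the EDD assigned by ANC providers using the best obstetric estimate". The next sentence is: "In health centers randomized to implement basic obstetric ultrasound, this tool will be used to optimize GA assignment". Correction by newborn measurements follows, for GA at birth.
- **The outcome.** Table 2 lists "Attendance at ANC one <14 weeks GA" as a secondary outcome, compared across arms, with ANC 1 as its time point. Table 3 gives "Women who attended ANC 1 <16 weeks", among all women who attended ANC 1, with the ANC Register as source.
- **Planned use.** Study aims includes the effect of ultrasound and pregnancy testing on ANC attendance. The Discussion promises insight into the relative effects of ultrasound and "urine pregnancy testing at the community level on early uptake of ANC". Statistical analyses makes Arms 1+2 v 3+4 the main comparison and adds subanalyses by arm.
- **Background.** The Introduction reports that 56% of women enter ANC before 16 weeks. It also warns that GA estimates are problematic because early ultrasound is not routine.

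**The concern.** The package that is meant to bring women to care earlier also changes the tool that decides whether they came early. If the recorded GA at ANC 1 reflects the scan where there is one and other dating elsewhere, the same calendar visit can be counted as early in one arm and late in another. Randomisation does not remove this, because the measurement method is itself assigned. Recruiting more women or more facilities does not remove it either.

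What is at stake is one named secondary conclusion: whether ultrasound plus community testing leads to earlier ANC. Earlier attendance is the stated goal of the community testing. A systematic dating difference could produce an apparent effect, or cancel a real one, with no woman having come a day sooner or later.

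**Working it through.** **1. Which contrasts are exposed**

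| Contrast | Ultrasound on first side | Ultrasound on second side |
|---|---|---|
| 1+2 v 3+4 (main) | one arm of two | one arm of two |
| 2+4 v 1+3 (package) | both arms | neither |
| 2 v 1; 4 v 3 | yes | no |

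The main contrast is balanced by design. The others are not.

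**2. The plan's own sample-size figure**

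The plan gives no size calculation for early attendance. Its figure for GA at birth reproduces. The inputs are SD 4.3 weeks, difference 0.5 week, ICC 0.01 and 18 facilities a side, at two-sided 5% and 80% power. With t quantiles on 34 df, the requirement is 214.1 per facility. Then 214/0.70 = 306 and 306 × 36 = 11,016. These figures neither support nor weaken the present point; 306 per facility is used below.

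**3. Effect of a mean dating difference**

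*From the document:* 56% before 16 weeks. *Assumed:* GA at ANC 1 is normal with SD s of 4-7 weeks; mean dating differs by b weeks between methods; every woman in Arms 2 and 4 is scanned; attendance is identical in all arms.

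Mean: μ = 16 − z(0.56) × s. Change in proportion: Φ((c − μ − b)/s) − Φ((c − μ)/s), with c = 14 or 16.

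| s (weeks) | μ (weeks) | Change for b = ±0.5 week (points) | Change for b = ±1 week (points) |
|---|---|---|---|
| 4 | 15.40 | 4.6-5.0 | 8.9-9.9 |
| 5 | 15.25 | 3.8-4.0 | 7.5-8.0 |
| 6 | 15.09 | 3.2-3.3 | 6.4-6.6 |
| 7 | 14.94 | 2.8 | 5.6-5.7 |

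Each cell shows absolute size over both cutoffs and both signs. A half-week difference gives 2.8-5.0 points and one week 5.6-9.9 points.

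**4. Partial uptake of a voluntary scan**

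Multiply by the share scanned (assumed 50-70%). The lower end is 0.50 × 5.6 = 2.8 points and the upper end 0.70 × 9.9 = 6.9 points: about 3-7 points per week of dating difference.

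**5. Same mean, different precision**

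*Assumed:* ultrasound error SD 0.7 week, other dating error SD 1-3 weeks, no bias, s = 4-6. The proportion below c is Φ((c − μ)/√(s² + e²)). The largest change is at s = 4, c = 14, e = 3: 36.5% with ultrasound against 39.0% without, a difference of 2.5 points.

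**6. Compared with the precision of the package contrast**

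SE = √[2 × 0.56 × 0.44 × (1 + 305 × ICC)/(18 × 306)], with 18 facilities a side and 306 women in each.

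| ICC | 1 + 305 × ICC | SE (points) | One-week artefact, full uptake |
|---|---|---|---|
| 0.01 | 4.05 | 1.9 | 2.9-5.2 SE |
| 0.02 | 7.10 | 2.5 | 2.2-3.9 SE |
| 0.05 | 16.25 | 3.8 | 1.5-2.6 SE |

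The document gives ICC 0.01 for GA at birth only. All three ICC values are assumptions for this outcome.

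**The case against.** **The dating sentence is about another outcome.** It follows the definition of GA at birth. No sentence says that a scan-based due date reclassifies GA at ANC 1. This stands: a reader might infer that the plan prescribes ultrasound dating of ANC 1 in Arms 2 and 4, but it does not state that. What the documents support is that such dating is possible, since the scan may be done on the day of that visit and exists to set the due date.

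**There is a shared source.** Table 3 names the ANC Register in every arm, Table 2 fixes the time point at ANC 1, and ultrasound findings go on a separate form. One natural reading is that the register holds a pre-scan GA. That reading would shrink the problem, but nothing secures it. A common register is not a common dating method, and the article does not say whether the entry precedes or follows a same-day scan.

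**The consequence is limited.** The main comparison is balanced, a pooled 2+4 v 1+3 contrast is not named in Statistical analyses, and this is one secondary outcome among several. A reader might infer that the whole early-attendance result cannot be interpreted. The documents do not support that; only contrasts that differ in ultrasound are exposed. Those contrasts do, however, answer a stated secondary aim.

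**The size is assumed.** The SD, the dating difference, the uptake and the ICC for this outcome are not in the documents, and neither is the sign. This stands in full, and the figures are scenarios.

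**The article is condensed.** An operational dating rule could sit in an analysis plan. But the article itself fixes this outcome's cutoff, time point, denominator and source, and separately makes the dating tool depend on arm. That combination is a weakness in what is stated.

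**Conclusion.** The point holds for the package contrast (Arms 2+4 v 1+3) and for the arm-level contrasts 2 v 1 and 4 v 3. It does not hold for the main contrast. In the exposed comparisons the plan allows the dating method to differ with assignment, and no rule ties early attendance to a common source recorded before the scan.

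Under the assumptions stated above, a one-week mean difference in dating would shift the early-attendance proportion by about 6-10 points at full scan uptake, or about 3-7 points at 50-70% uptake. If the methods differ only in precision, the shift is at most about 2.5 points. If the register's GA is always entered before any scan, and in the same way in all arms, the artefact largely disappears. Whether a bias exists, and in which direction, cannot be determined from the documents.

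This should be fixed, because a planned conclusion about early uptake depends on it. The primary outcome analysis is outside this point.

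**What to change.** For early ANC attendance:

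1. Classify GA at ANC 1 in all four arms from the same non-ultrasound source recorded before any scan: LMP, or the pre-scan register entry.
2. State in Tables 2 and 3 that later re-dating does not change this outcome.
3. Report the ultrasound-based classification in Arms 2 and 4 as a sensitivity analysis.
4. Reconcile the cutoff, which is below 14 weeks in Table 2 and below 16 weeks in Table 3, and use one definition throughout.
5. Report completeness of the chosen source by arm.

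The cost is a short change to the outcome definition and a recode, provided LMP or a pre-scan GA is held for ANC 1. Table 3 mentions an LMP-calculated GA only for GA at birth, so this must be confirmed first. LMP is noisier and sometimes missing. That loss need not be equal across arms, because community testing or a same-day scan could affect how LMP is recalled or recorded; hence step 5.
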